“Bariatric surgery for non-alcoholic Fatty Liver Diseases in Individuals with Obesity (Base-NAFLD)” is a prospective multicentre observational follow-up study. This study aims to adequately assess the effect of bariatric surgery on NAFLD remission in obese patients: (i) to demonstrate the effectiveness of bariatric surgery for NAFLD, including NASH, (ii) to explore the differences in the effectiveness among three types of surgery—sleeve gastrostomy (SG), Roux-en-Y gastric bypass (RYGB), and one anastomosis gastric bypass (OAGB), and (iii) to develop a predictive model for surgical treatment using internal and external validation cohorts. This study will provide a necessary and preliminary foundation for the early identification and targeted treatment of patients with NAFLD, who need to be referred for bariatric surgery for the management of obesity and metabolic diseases.

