## Methods

### Patient recruitment

The Base-NAFLD study is a prospective, multicentre, observational study. Patients scheduled to undergo one of the three types of bariatric surgery—SG, RYGB, and OAGB—at the participating centres, between 21 April and 31 December 2020, will be screened for consecutive enrolment in this study. The corresponding follow-ups will be conducted 2 years postoperatively until December 2022.

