### Sample size determination

The Power Analysis and Sample Size software program (PASS, version 11.0 by NCSS, LLC) was used for sample size calculation, which was based on the estimated complete remission rate reported by previous retrospective studies [9–12] and the preliminary clinical results obtained from our centre. According to our preliminary data, 58 of the 69 patients (84%) who underwent bariatric surgery had preoperative underlying NAFLD, and the rate of complete remission was 55.2% three months postoperatively. To achieve a confidence interval width of 0.16 and an α value of 0.05 with a 78% complete remission rate, the estimated minimum sample size required for our study was 114. The withdrawal rate will be assumed to be 20% during follow-up; therefore, the sample size needed for this study will be at least 142 patients. Nevertheless, as this is an observational study, additional patients will be recruited for a subgroup analysis. According to the national registry in our country, the number of patients undergoing each type of surgery was found to be 82, 30, and 30 patients for the SG, RYGB, and OAGB groups, respectively.

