### Statistical analysis

SPSS 20.0 (SPSS, Inc., Chicago, IL, USA) and R software (R version 3.6.3; R Foundation for Statistical Computing, Vienna, Austria) will be used to perform statistical analyses. Continuous data will be presented as mean (standard deviation) or median (minimum, maximum) values, and categorical data will be presented as numbers (proportions/frequencies/percentages). P-values < 0.05 will be considered statistically significant.Comparison between preoperative and postoperative parameters: For paired continuous data, the paired t-test (normally distributed variables) or Wilcoxon’s signed-rank (skewed variables) will be used for analysis, whereas for paired categorical data, the chi-square test or Fisher’s exact test will be used for analysis.Primary outcomes: The complete remission rate of NAFLD in obese patients, along with the corresponding 95% confidence interval will be reported.Sensitivity analysis: A sensitivity analysis will be conducted to investigate the differences between the three types of surgery and BMI subgroups in terms of complete remission rate of NAFLD. Continuous variables will be tested by a paired t-test or Wilcoxon’s signed-rank test for paired samples, and the association between covariates and main outcomes will be tested using the chi-square test or Fisher’s exact test.Development and validation of the prediction model: Before building the model, the dataset will be divided into a training set—three-quarters of the enrolled patients will be randomly assigned to this set—and a validation set—the remainder of the patients will be assigned to this set. A multivariable logistic regression model will be used in which the response variable will be complete remission of NAFLD. The model will be built using stepwise selection based on the Akaike information criterion. The training model will be subsequently applied to the validation set. The model performance of both the training and validation sets will be evaluated using C statistics for discrimination, and the goodness-of-fit will be evaluated using Hosmer–Lemeshow test. A calibration curve will also be developed to examine the model fit. For both the training and validation sets, the predicted risk will be plotted against the observed risk for each of the 10 risk percentiles created from the dataset. Calibration will be evaluated using the Hosmer–Lemeshow goodness-of-fit test and chi-square test based on the predicted risk deciles. Results will be displayed as a nomogram to provide clinicians with an intuitive and quantitative tool to predict the probability of complete NAFLD remission in obese patients.

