To the best of our knowledge, this is the first prospective multicentre observational follow-up study that will adequately assess the usefulness of bariatric surgery, including three mainstream surgical procedures, on NAFLD remission in patients. By exploring the primary and secondary outcomes, the risk factors that strongly contribute to complete NAFLD remission will be identified to develop and verify the predictive model. This study will also provide preliminary results on the optimal choice of surgery type for patients with NAFLD as the presence of NAFLD in obese patients is not a definite indication for bariatric surgery worldwide according to the current clinical guidelines. Moreover, by investigating the preoperative factors associated with complications, we will be able to identify modifiable factors to prevent complications in the future. In summary, this study will improve our understanding of NAFLD development in obese patients and identify the factors influencing its outcomes, facilitating the optimisation of individualised treatment and eventually providing high-quality evidence for the indication of bariatric surgery for NAFLD.

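### The comparison of remission across the three non-randomised procedures has only a crude chi-square or Fisher test, so it is open to confounding by baseline liver fat and BMI

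*Protocol article*

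**What the plan says.** The Patient recruitment section sets the design: "The Base-NAFLD study is a prospective, multicentre, observational study". Patients are enrolled once they are already scheduled for one of the three procedures, so procedure is not assigned by the study.

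The Background lists as its second aim "to explore the differences in the effectiveness among three types of surgery". The Discussion says: "This study will also provide preliminary results on the optimal choice of surgery type for patients with NAFLD".

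In the Statistical analysis section the comparison appears as a sensitivity analysis, meant to "investigate the differences between the three types of surgery and BMI subgroups in terms of complete remission rate of NAFLD". Two kinds of test follow. Continuous variables get a paired t-test or Wilcoxon signed-rank test, and "the association between covariates and main outcomes will be tested using the chi-square test or Fisher’s exact test". BMI enters as a subgroup factor, not as an adjustment variable.

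The same section also plans a prediction model: "A multivariable logistic regression model will be used in which the response variable will be complete remission of NAFLD". It is fitted in a random three-quarters of the patients, and "The model will be built using stepwise selection based on the Akaike information criterion".

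The Outcome measures section defines remission as LFF below 5% on MRI at one year. The Data collection section lists preoperative LFF from MRI, height, weight and diabetes history. Table 1 marks abdominal MRI as mandatory at baseline.

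**The concern.** When clinicians and patients choose the operation, the groups may differ before surgery in ways that also affect remission. Baseline liver fat is the clearest candidate because the endpoint is a fixed threshold: for the same reduction, a patient who starts lower is more likely to finish below 5%. Starting values can vary widely, since entry requires only steatosis on ultrasound, MRI or pathology.

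A crude contingency-table test cannot separate the effect of the operation from the starting level. A difference could then be read as preliminary evidence on which procedure to choose when it reflects only who received which operation. Equally, a real difference could be hidden. The article names the test, so this is a stated method that can be improved, not a detail left to a fuller document.

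**Working it through.** **1. The plan's own figure.** The sample size rests on one overall proportion: 78% remission and a 95% interval of full width 0.16. The exact (Clopper-Pearson) width is 0.1601 at n = 113 and 0.1594 at n = 114, so the stated 114 is reproduced. Then 114 / 0.8 = 142.5, against the stated 142. This size was set for a single rate, not for contrasts between procedures.

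**2. Which named analysis could compare the procedures?**

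| Analysis in the Statistical analysis section | Compares independent groups? | Adjusted for baseline? |
|---|---|---|
| Paired t-test, Wilcoxon signed-rank | No | No |
| Chi-square or Fisher's exact | Yes | No |
| Stepwise logistic prediction model | Only if procedure is a candidate and survives selection | Only for whatever selection keeps |

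The prediction model does not fill the gap. It uses three-quarters of the patients, it may drop procedure, LFF or BMI, and no adjusted procedure effect is described as an output.

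**3. Size of a spurious gap.** The documents give no baseline data by procedure, so every input in this step is an assumption. Suppose procedure has no effect, and remission is 85% with low and 65% with high baseline LFF. Let the high-LFF share be 40% in SG and 70% in RYGB.

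- SG: 0.6 × 0.85 + 0.4 × 0.65 = 0.77
- RYGB: 0.3 × 0.85 + 0.7 × 0.65 = 0.71
- Gap: (0.70 − 0.40) × (0.85 − 0.65) = 0.06

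**4. False-positive rate of the crude test.** These are simulated trials with no procedure effect, groups of 82/30/30 as in the Sample size determination section, and a three-group Pearson chi-square at 0.05. The high-LFF shares and stratum rates are again assumed.

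| High-LFF share, SG/RYGB/OAGB | Remission low vs high LFF | Crude gap | Crude test rejects |
|---|---|---|---|
| 50/50/50% | 88% vs 68%, or 93% vs 63% | 0 | about 5% |
| 40/60/60% | 88% vs 68% | 0.2 × 0.2 = 4 points | 8% |
| 40/60/60% | 93% vs 63% | 0.2 × 0.3 = 6 points | 12% |
| 30/70/70% | 88% vs 68% | 0.4 × 0.2 = 8 points | 18% |
| 30/70/70% | 93% vs 63% | 0.4 × 0.3 = 12 points | about 35% |

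A logistic test of procedure adjusted for the stratum rejected about 6% of the time in every scenario. With 20% withdrawal the groups are about 66/24/24 (82 × 0.8 = 65.6; 30 × 0.8 = 24). The crude test then rejects 5% to 29% of the time and the adjusted test about 5% to 7%. Some simulated maximum-likelihood fits did not converge, which is a reason to penalise.

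**5. Room for covariates.** Expected non-remitters: 114 × 0.22 ≈ 25, of whom 24 × 0.22 ≈ 5 are in each of RYGB and OAGB. Two procedure terms plus LFF and BMI make four parameters, or about 25 / 4 ≈ 6 non-remitters per parameter. A fifth term brings this to 5.

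**The case against.** **Confounding is not demonstrated.** A reader might infer that the groups will differ in LFF and BMI and that the comparison is therefore biased. Nothing in the article says how the procedure is chosen, and no baseline data by procedure are given. This objection stands: the exposure to bias follows from the design, but its presence and direction do not.

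**A multivariable model exists.** A reader might infer that remission is never modelled jointly with covariates. That would be wrong, and procedure, LFF and BMI are plausible candidates for the prediction model. But the model is not set up to estimate a procedure effect, so the objection limits the wording and not the point.

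**The comparison is already modest in its claims.** The aim is to explore, the analysis is called a sensitivity analysis, and the Discussion promises preliminary results. This stands and lowers the stakes. An exploratory label does not, however, remove a bias that the collected data could reduce.

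**The numbers may be small.** With 66 and 24 patients, a 77% vs 71% gap has a standard error of √(0.77 × 0.23/66 + 0.71 × 0.29/24) ≈ 0.106. It would reach p < 0.05 only about 9% of the time. The larger rates in the table need the more extreme 30/70/70% split. This stands.

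**Subgroup recruitment.** Because 82 + 30 + 30 = 142, a reader might infer that the promise that "additional patients will be recruited for a subgroup analysis" is empty. The text gives 142 as a minimum, and 82/30/30 can be read as the split of that minimum, so no contradiction is shown. Small groups are also a separate matter. At 78% remission the exact interval is 0.21 wide for 66 patients and 0.36 for 24, and power for 78% vs 58% (66 vs 24) is about 47%. Adjustment would not change that.

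**Conclusion.** The point holds in a limited form. A stated aim is a comparison of non-randomised groups, and the only named test able to make it is unadjusted, although the main candidate confounders are already collected. The comparison is open to confounding by baseline LFF and BMI.

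The size cannot be fixed from the documents. Under the assumed imbalances the spurious gap is 0 to 12 percentage points, and the crude test's false-positive rate is 5% (balanced groups) to about 35% (strong imbalance and a strong LFF effect). The moderate 40/60/60% split gives 8% to 12%.

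The overall remission rate with its 95% interval, and the sample size of 142, are untouched. The change is worth making before analysis, but it concerns an exploratory aim and not the primary result.

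**What to change.** In the sensitivity-analysis text of the Statistical analysis section, replace the chi-square or Fisher test as the analysis of the procedure comparison with one prespecified regression:

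- Outcome: complete remission at one year, in all evaluable patients and not only the training set.
- Procedure forced in, with no stepwise selection.
- A small fixed adjustment set led by baseline LFF and baseline BMI, both continuous.
- A penalised fit, for example Firth logistic regression, because only about 25 non-remitters are expected among 114.
- Adjusted risk differences between procedures with 95% intervals, labelled exploratory, with crude rates alongside.

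Keep the prediction model as a separate analysis, and leave the recruitment wording in the Sample size determination section as it is.

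The cost is wording only, since the covariates are already collected. The downside is that few covariates can be carried, so other differences such as centre may remain unadjusted, and the intervals will be wide.

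### The random 3:1 split leaves a validation set of about 28 to 36 patients, too few to judge discrimination or decile calibration; bootstrap validation on all patients is better

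*Protocol article*

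**What the plan says.** The model paragraph of the protocol article's Statistical analysis section divides the data at random before any modelling: "three-quarters of the enrolled patients will be randomly assigned to this set" (training), and "the remainder of the patients will be assigned to this set" (validation). The response is complete remission of NAFLD in a multivariable logistic regression. On selection it says: "The model will be built using stepwise selection based on the Akaike information criterion". Both sets are then assessed by the C statistic, the Hosmer-Lemeshow test and a calibration curve. On the last of these, "the predicted risk will be plotted against the observed risk for each of the 10 risk percentiles created from the dataset", with a further chi-square test on the predicted-risk deciles. The result is to be shown as a nomogram for clinicians.

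The Sample size determination section sizes the study only for the precision of the remission rate: "To achieve a confidence interval width of 0.16 and an α value of 0.05", and "with a 78% complete remission rate, the estimated minimum sample size required for our study was 114". It adds: "The withdrawal rate will be assumed to be 20% during follow-up", which gives at least 142 enrolled. It also foresees extra patients for a subgroup analysis, without a number. The model has no sample size of its own.

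The aims in the Background name internal and external validation cohorts. The Statistical analysis section describes only the random split.

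**The concern.** A sample chosen to estimate one proportion is cut in four, and one quarter has to carry the whole validation. What limits a binary-outcome model is the size of the rarer group, here the non-remitters. At 78% remission they are 22% of patients, so the validation set holds only a handful. Ten risk groups spread that handful thinner still.

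The third aim of the study and its nomogram are at stake. If the validation C statistic is compatible with anything from near chance to near perfect, it neither supports nor refutes the model. If the decile tests neither hold their nominal level nor reliably detect poor calibration, neither a pass nor a failure can be interpreted. The split also withholds a quarter of a small dataset from model fitting.

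**Working it through.** **Inputs from the document.** Evaluable minimum 114; enrolled at least 142; remission 78%; pilot remission 55.2% at three months (used only as a range); training share 3/4; ten risk groups. **Assumed:** a true C of 0.75, and the spread of the linear predictor in the simulation.

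**1. The plan's own figure.** The exact (Clopper-Pearson) 95% interval at p = 0.78 first has width at or below 0.16 at n = 114 (width 0.1594), which matches. Withdrawal: 114 / 0.8 = 142.5, against 142 stated; the difference does not matter here.

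**2. Size of the two sets at 114 evaluable, 78% remission.**
- Validation: 114 × 0.25 = 28.5 patients; × 0.22 = 6.3 non-remitters (95% binomial range about 2 to 11).
- Per decile: 28.5 / 10 = 2.85 patients and 0.63 non-remitters.
- Training: 114 × 0.75 = 85.5 patients; × 0.22 = 18.8 non-remitters.
- All patients: 114 × 0.22 = 25.1 non-remitters.

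**3. Range over the document's other figures.**

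| Evaluable | Remission | Validation n | Non-remitters | Patients per decile |
|---|---|---|---|---|
| 114 | 78% | 28.5 | 6.3 | 2.85 |
| 142 | 78% | 35.5 | 7.8 | 3.55 |
| 114 | 55.2% | 28.5 | 12.8 | 2.85 |
| 142 | 55.2% | 35.5 | 15.9 | 3.55 |

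**4. Precision of the validation C statistic (Hanley-McNeil).** With m positives and n negatives,

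SE² = [C(1−C) + (m−1)(Q1−C²) + (n−1)(Q2−C²)] / (mn), where Q1 = C/(2−C) and Q2 = 2C²/(1+C).

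At C = 0.75: Q1 = 0.6000, Q2 = 0.6429, C² = 0.5625. The formula is not symmetric in the two classes, so both versions are shown for 6.27 non-remitters and 22.23 remitters (mn = 139.4).
- Remission as positive class (the plan's response): (0.1875 + 21.23 × 0.0375 + 5.27 × 0.0804) / 139.4 = 0.0101; SE 0.10; 95% CI 0.55 to 0.95.
- Non-remission as positive class: (0.1875 + 5.27 × 0.0375 + 21.23 × 0.0804) / 139.4 = 0.0150; SE 0.12; 95% CI 0.51 to 0.99.

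In the three more favourable rows of the table the SE is about 0.08 to 0.11. The non-remission version gives intervals of 0.54 to 0.96 (142, 78%), 0.56 to 0.94 (114, 55.2%) and 0.58 to 0.92 (142, 55.2%).

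On all 114 patients the same formula gives an SE of about 0.05 to 0.06, roughly half. That figure leaves out the uncertainty in the optimism correction.

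**5. Decile Hosmer-Lemeshow test at n = 28 (simulation).** Over the assumed linear-predictor spreads, it rejects about 7 to 14% of the time when calibration is perfect (nominal 5%). It rejects only about 13 to 37% of the time when the true calibration slope is 0.5, which is marked overfitting. At a spread (SD) of 1.1 the two rates are about 10% and 23%.

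**The case against.** The strongest reply is that 114 is a minimum. The plan says at least 142 and foresees extra recruits, and 78% is only a planning value. This stands as a reason to make the counts conditional: fewer than three patients per decile holds at 114, but the figure is about 3.6 if nobody withdraws. It does not rescue the split. Even at an assumed 300 evaluable patients, 300 × 0.25 × 0.22 = 16.5 non-remitters would be in the validation set, and the half-width of the C interval would be about 0.15 on the wider version.

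Several stronger readings are tempting, and the document does not support them.
- *The C interval reaches 1.00.* At C = 0.75 this comes from treating non-remission as the positive class and rounding the counts to 6 and 22. With the plan's own response the upper limit is about 0.95.
- *The Hosmer-Lemeshow test has almost no power.* The power is low, at about 13 to 37%, and the test also rejects too often under perfect calibration. That the authors would report a non-significant result as good calibration is a guess; the plan also has a calibration curve.
- *A stated amount of overfitting.* The data collection section lists what is recorded, not which variables enter selection. An article may leave the candidate list to a fuller document, so any simulated degree of overfitting would rest on an invented number of candidates.
- *Bootstrapping solves the problem.* It does not add non-remitters, and it gives internal validation only.

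It is also fair that the model is the third aim of a study that calls itself preliminary. That bears on priority; the arithmetic is unchanged.

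**Conclusion.** The point holds for the split and the decile checks, both of which the article itself fixes. Under every sample size and remission rate it states, the validation set has about 28 to 36 patients and about 6 to 16 non-remitters. The SE of its C statistic, for an assumed true value of 0.75, is about 0.08 to 0.12. At the planning values the interval runs from little better than chance to nearly perfect, and with 0.6 non-remitters per decile the calibration plot and tests carry little information.

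The counts follow directly from the document. The C-statistic precision rests on the assumed true C and the Hanley-McNeil approximation, and the test rejection rates on assumed linear-predictor spreads. The finding concerns the model and its nomogram and should be acted on. It does not touch the primary remission rate or its confidence interval.

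**What to change.** - Develop the model on all evaluable patients and drop the random split.
- Validate by bootstrap optimism correction, repeating every modelling step, including variable selection, in each resample.
- Report the optimism-corrected C statistic, the calibration slope and intercept, and a smoothed calibration curve. These replace the decile plots and the Hosmer-Lemeshow and decile chi-square tests.
- Limit the candidate predictors to a small prespecified set suited to about 25 to 31 non-remitters (114 × 0.22 to 142 × 0.22). Shrinkage is an option; the choice of method is the sponsor's.
- State that this is internal validation only, and either specify the external cohort named in the aims or reword that aim.

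The cost is protocol and analysis-plan wording and some recoding in R, which the plan already uses. No new data are needed for the internal validation. The downside is that there will be no separate hold-out figure to report. The small number of non-remitters remains the main limit on the model.

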### Data collection

A standard case report form was designed before the study and transferred to an electronic data capture (EDC) system (https://www.base-nafld.com). The EDC system provides a graphical user interface for data entry and has a validation component for data cross-checking and a reporting tool for descriptive analysis. Well-trained clinical research coordinators from Chuankang (Medicine Technology Co, Beijing, China) and Suzhou Plenitude (Bio-Medical Technology Co., Ltd., Jiangsu, China) will retrieve all required information from the medical records of included patients and upload them into the EDC system. Clinical research associates from Beijing Funhau Medicine Technology Co. are in charge of monitoring and providing feedback on the EDC system and for data quality control.

The case report form was designed to collect the following baseline and follow-up data (Table 1):Demographic data: study code, initial name, sex, date of birth, admission date, height, body weight, transumbilical abdominal circumference, smoking habits, and drinking habits.Disease history and medication usage: type 2 diabetes mellitus, hypertension, polycystic ovarian syndrome, and obstructive sleep apnoea hypopnoea syndrome; use of oral hypoglycaemic, insulin, anti-hypertensive medication, and lipid-lowering drugs.Preoperative examinations: routine blood tests and biochemical examinations, especially for ALT, AST, HbA1c, fasting blood glucose, fasting insulin levels, prothrombin activity time, and AFP; findings from abdominal ultrasonography and gastroscopy; and assessment of LFF levels from MRI.Surgical information: operation date, type of surgery, operation time, and surgical procedure information, including gastric pouch volume, Roux limb length, biliopancreatic limb length, stapler usage, and suturing.Liver pathology: findings from histopathological examinations of liver biopsy specimens obtained intraoperatively and one year postoperatively.Adverse events or serious adverse events.

**Table 1 Tab1:** Checklist of baseline and follow-up visits of patients enrolled in the Base-NAFLD study

	Visit 1 (Baseline)	Visit 2 (3-month intervals)	Visit 3 (6-month intervals)	Visit 4 (1-year intervals)	Visit 5 (2-year intervals)
Demographic data	●	●	●	●	●
Disease history and medication usage	●	●	●	●	●
Surgical information	●	✗	✗	✗	✗
Weight loss	✗	●	●	●	●
Routine blood tests	●	●	●	●	●
HbA1c	●	●	●	●	●
OGTT	●	✗	✗	○	✗
FBG	✗	●	○ ●	✗	●
Fasting insulin and fasting C-peptide	✗	○	○	●	○

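### AIC stepwise selection, with no shrinkage or cap on terms stated, is a poor rule for building the remission model from about 19 training non-remitters: it readily keeps null factors and gives over-extreme predictions

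*Protocol article*

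**What the plan says.** The Statistical analysis section of the protocol article plans a multivariable logistic regression with complete NAFLD remission as the response. On the choice of terms it says: "The model will be built using stepwise selection based on the Akaike information criterion". The model is developed in a random training set ("three-quarters of the enrolled patients will be randomly assigned to this set"), and then "The training model will be subsequently applied to the validation set", with C statistics, Hosmer-Lemeshow tests and calibration plots by tenths of predicted risk. The result is to be offered to clinicians as a nomogram.

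The same section separately plans univariable tests: "the association between covariates and main outcomes will be tested using the chi-square test" (or Fisher's exact test), under the general rule "P-values < 0.05 will be considered statistically significant". These tests are not linked to the choice of model terms.

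The Discussion says how the results will be read: "the risk factors that strongly contribute to complete NAFLD remission will be identified to develop and verify the predictive model".

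The Sample size section supplies the planning figures: "with a 78% complete remission rate, the estimated minimum sample size required for our study was 114", raised to at least 142 for 20% withdrawal. No candidate list is given. The Data collection section only describes what is recorded: "The case report form was designed to collect the following baseline and follow-up data (Table 1").

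**The concern.** Two separate weaknesses meet in this one sentence of the plan.

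- **Selection.** AIC is a lenient threshold for a single term. Applied to many candidates, it will often keep variables unrelated to remission, and the Discussion would then present retained variables as strong contributors.
- **Overfitting.** Remission is expected in 78%, so the limiting outcome group is the non-remitters, and there are few of them. Data-driven selection followed by unpenalised fitting in so small a group gives coefficients that are too large and predicted probabilities too close to 0 or 1.

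At stake are aim (iii), the predictive model, and a nomogram meant for individual patients. The primary outcome, a remission rate with its 95% confidence interval, does not depend on this model.

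**Working it through.** **1. The plan's sample size.** The exact (Clopper-Pearson) 95% interval at 78% has full width 0.1601 with n = 113 and 0.1594 with n = 114. So 114 is reproduced as the first n with width at most 0.16. For withdrawal, 114 / 0.8 = 142.5, stated as 142.

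**2. Non-remitters available.** Inputs: 114 evaluable, 78% remission, three-quarters for training.

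| | 114 evaluable | all 142 evaluable |
|---|---|---|
| Training patients | 0.75 × 114 = 85.5 | 0.75 × 142 = 106.5 |
| Training non-remitters (× 0.22) | 18.8 | 23.4 |
| Validation patients | 28.5 | 35.5 |
| Validation non-remitters (× 0.22) | 6.3 | 7.8 |

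**3. AIC threshold for one term.** Adding one parameter lowers AIC when the likelihood-ratio chi-square exceeds 2. For a null term, P(chi-square on 1 df > 2) = 0.157.

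**4. Number of candidates (assumption).** None is stated. Counting from the Data collection list: 7 demographic and habit items (sex, age, height, weight, circumference, smoking, drinking), 4 diseases, 4 drug classes, 7 named laboratory tests, liver fat fraction and type of surgery give 7 + 4 + 4 + 7 + 1 + 1 = 24. This shows that 20 is possible, not that it is planned, so 5, 10 and 20 are shown.

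**5. Chance of keeping at least one factor when none has an effect.** For k independent candidates this is 1 − (1 − 0.157)^k. The simulation used 85 patients with 19 non-remitters, 1,000 runs per setting, and equal pairwise correlation of 0, 0.3 or 0.5. The range covers all-continuous and part-binary candidates.

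| Candidates | Formula, independent | Simulated range |
|---|---|---|
| 5 | 57.5% | 51-60% |
| 10 | 81.9% | 66-84% |
| 20 | 96.7% | 85-97% |

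With 20 null candidates, stepwise selection from the empty model kept about 3.7 on average when they were independent and about 2.6 at correlation 0.5. A 60-run check starting from the full model kept at least one in 98% of runs and about 4.5 on average.

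**6. Predictions in new patients.** Illustrative assumption: two real predictors (log-odds 0.8 and 0.5 per SD), the other candidates null, 78% remission, 86 training patients, stepwise AIC, 120 runs per setting.

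- 20 independent candidates: 5.0 terms kept, 3.5 of them null. C statistic 0.84 in training and 0.64 in new patients; calibration slope 0.29 (0.33 at correlation 0.3).
- 10 candidates: slope 0.47 independent, 0.57 at correlation 0.3.
- All 142 evaluable (107 in training), correlation 0.3: slope 0.41 with 20 candidates, 0.61 with 10.

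Across repeated simulations at the planned size, the slope was about 0.2-0.35 with 20 candidates and about 0.5 with 10.

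**7. Penalised alternative under the same effects.** Ridge on all 20 candidates gave C 0.63 and slope 1.10, against C of about 0.65 for stepwise. Ridge on five variables that include both real ones gave C 0.70 and slope 1.11. Ridge on five variables that miss one real predictor still gave lower log-loss than stepwise. Ridge slopes ran from about 1.0 to 1.4, so it tends to shrink slightly too much.

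**8. Can the held-out set catch it?** It has about 28.5 patients and 6.3 non-remitters. Split into tenths of risk, that is 2.85 patients and 0.63 non-remitters per group. It also checks the model as a whole, not any single factor.

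**The case against.** Four stronger readings are tempting, and the article does not support them.

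- **That AIC is the only rule identifying factors for remission.** It is not: chi-square or Fisher tests of covariates are also planned. AIC is only the sole stated rule for choosing terms in the multivariable model. The univariable tests do not rescue it: no multiplicity rule is stated, and 20 independent null tests at 0.05 would yield at least one finding 1 − 0.95^20 = 64% of the time.
- **That a false factor appears 97% of the time.** That needs 20 independent candidates, all null. The article fixes no number, the recorded variables are plainly correlated (ALT with AST, HbA1c with glucose), and a complete null is hard to credit when baseline liver fat fraction is recorded and the outcome is a liver fat threshold. The candidate list may sit in an analysis plan that is not shown, so its absence is no fault here.
- **That the 97% comes from having 19 non-remitters.** It comes from the AIC threshold and the number of candidates. The small outcome group drives the overfitting, which is a separate harm.
- **That 19 is certain.** It is a planning figure. The article allows for additional patients, and at the pilot's three-month remission rate of 55.2%, 86 patients would include 86 × 0.448 = 38.5 non-remitters.

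It is also fair to say that AIC aims at predictive fit and promises no 5% error rate, that held-out validation is planned, and that the Background mentions an external validation cohort. The effect sizes in the simulation are invented, and with the same 20 candidates ridge did not improve discrimination. These points limit the size of the claim. They leave the main point standing: the selection method is stated, and its predictions were too extreme in every setting tried with real predictors, including 10 correlated candidates and full retention. Validation measures that failure but does not correct it.

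**Conclusion.** The point holds in a conditional form, limited to the multivariable model. AIC stepwise selection without stated shrinkage or a cap on terms is a poor choice at this sample size.

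The per-term null retention rate of 15.7% is exact in large samples. The chance of at least one null factor (51-60%, 66-84% and 85-97% for 5, 10 and 20 candidates) rests on an assumed candidate number, pairwise correlation between 0 and 0.5, and no real effects. The calibration slopes (about 0.2-0.35 with 20 candidates, about 0.5 with 10) rest on the planning figures and the illustrative effects; full retention of 142 improves them to 0.41 and 0.61 at correlation 0.3. The Discussion's reading of retained variables as strong contributors is not earned by this rule. The change should be made, but the primary result does not depend on it.

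**What to change.** In the Statistical analysis section, replace the stepwise AIC sentence with wording such as: about five preoperative predictors, chosen on clinical grounds before outcome data are seen (for example baseline liver fat fraction, BMI, HbA1c or diabetes, age, planned procedure), will all be kept and fitted by penalised (for example ridge) logistic regression.

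If selection is retained, repeat the whole selection within each resample, and report how often each variable is selected together with optimism-corrected C statistic and calibration slope.

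In the Discussion, describe retained variables as predictors in the model, not as risk factors that contribute strongly to remission.

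The cost is analysis wording only: the example variables are already on the case report form or derive from it, and R is already named. The downside is that a real predictor left off the list will not enter the nomogram. The gain is mainly in calibration, with discrimination similar or modestly better.
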